### Study interventions

2.6

The interventions will be administered at two specific time points: 30 min before the induction of anesthesia and 5 min after tracheal extubation in the PACU, with each session lasting 30 min. Prior to the initiation of stimulation, the left auricle will be cleansed using gauze moistened with a saline solution. The unblinded coordinator will position the taVNS device (model taVNS501, Reshen Medical Technology Co., Ltd., Changzhou, China) according to the randomization assignment.

Participants assigned to the taVNS group will undergo stimulation at the left cymba conchae, an area innervated by the auricular branch of the vagus nerve. This stimulation will be administered using a pulse frequency of 20 Hz and a pulse width of 250 μs. The stimulus amplitude will initially be set to zero and will be gradually increased until the participant experiences a tolerable tingling sensation, typically within 30 s, which will be maintained throughout the 30-min session. In the sham group, the electrode placement will be identical to those of the active taVNS group using the same stimulation parameters. The stimulus amplitude will be incrementally increased until the participant perceives a tingling sensation after which the current will be immediately discontinued. The device will remain powered on, with identical auditory and visual cues, for the entire 30-min session to ensure the absence of sustained neuromodulatory effects while preserving participant blinding.

During each stimulation, participants will remain in a supine position while undergoing continuous monitoring through electrocardiography, pulse oximetry, and noninvasive blood pressure assessment. Trained personnel will provide constant observation of the participants. Stimulation will be immediately stopped if any of the following occur: (1) unbearable discomfort; (2) oxygen saturation (SpO_2_) drops below 90%; (3) heart rate falls below 50 beats per minute or decreases by more than 20% from the initial rate; (4) a new arrhythmia begins; (5) hemodynamic instability, defined as systolic blood pressure below 90 mmHg or above 180 mmHg; or (6) any significant adverse event. The attending physician will decide on the suitable clinical management.

### Outcomes

2.7

#### Main outcome

2.7.1

The primary endpoint is the incidence of POSD on POD 1, defined as an Athens Insomnia Scale (AIS) score ≥ 6. The AIS is a validated eight-item instrument measuring nocturnal sleep parameters and daytime functioning, with total scores ranging from 0 to 24 (22).

#### Secondary outcomes

2.7.2

Trajectory of Postoperative Sleep Quality (1) Subjective sleep quality: The trajectory of AIS total scores from Preoperative Day 1 (Pre-1) through POD 3. (2) Objective sleep parameters: Wrist actigraphy (HUAWEI WATCH GT2) measured continuously from Pre-1 through POD 3. Metrics include sleep continuity (latency, awakenings, wake after sleep onset, efficiency, and total sleep time) and sleep architecture (duration of light, deep, and REM sleep).Anxiety and Depression The Hospital Anxiety and Depression Scale (HADS) will evaluate anxiety (HADS-A) and depression (HADS-D) at Pre-1, POD 1, POD 2, and POD 3. Each subscale comprises seven items scored 0–3; scores ≥ 8 indicate probable anxiety or depression (23).Postoperative Pain and Recovery Quality Pain intensity will be assessed using the Numeric Rating Scale (NRS, 0–10) at rest and during movement on POD 1 (24). Analgesic consumption and patient-controlled analgesia demands will be recorded. Recovery quality will be evaluated on POD 1 using the 15-item Quality of Recovery (QoR-15) questionnaire (scores 0–150, higher scores indicating better recovery) (25).Quantitative EEG Parameters (1) Absolute power: The integral of the power spectral density (PSD) over respective frequency bands (delta 1–4 Hz, theta 4–8 Hz, alpha 8–12 Hz, beta 12–25 Hz, and gamma 25–45 Hz). (2) Peak frequency: The frequency at which maximum PSD occurs within each band.

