
### EEG power spectrum processing

2.5

Frontal quantitative EEG parameters will be obtained using the ConView YY-105 anesthesia depth monitoring system, employing bilateral frontal electrodes at a sampling rate of 500 Hz. EEG power spectral density will be estimated using the multitaper method (15 tapers, time-half bandwidth product = 8) with a 4-s window length and 50% overlap (2-s step), implemented in MATLAB’s pmtm function. The bandpass filter (0.5–45 Hz) will be applied as a zero-phase filter using forward-reverse filtering to avoid phase distortion. Artifact-free epochs will be extracted at six predetermined time points: T0 (pre-stimulation baseline): 5 min prior to the first taVNS session; T1 (preoperative sustained stimulation), 20–30 min following the initiation of taVNS; T2 (post-induction), 5 min after tracheal intubation; T3 (intraoperative maintenance), 20 min subsequent to the skin incision; T4 (peri-extubation), at the conclusion of surgery, immediately preceding emergence from anesthesia; and T5 (postoperative sustained stimulation), 20–30 min after the initiation of postoperative taVNS.

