### Statistical analysis

2.11

Statistical analyses will be performed using SPSS Statistics 26.0 (IBM Corp.) and R 4.4.0 (R Foundation). MATLAB R2018b (MathWorks, Natick, MA) will be employed for the preprocessing and spectral analysis of EEG data. Normality will be assessed using the Shapiro-Wilk test and Q-Q plots. Continuous variables will be presented as mean ± standard deviation or median (interquartile range), and categorical variables will be shown as frequencies and percentages.

The primary outcome (incidence of AIS ≥ 6 on POD 1) will be analyzed using the chi-square test to compare proportions between the taVNS and sham groups. The effect size will be expressed as an absolute risk reduction with a 95% confidence interval. Linear mixed-effects models will analyze repeated measures, including (1) AIS total scores (Pre 1 to POD 3); (2) HADS-A and HADS-D (as two separate scales, Pre 1 to POD 3); (3) objective sleep parameters from actigraphy; and (4) EEG spectral power across five bands (delta, theta, alpha, beta, and gamma) at six time points (T0–T5). Models include fixed effects for group, time, group × time interaction, and random intercepts for subjects. For repeated clinical outcomes, Bonferroni correction will be applied across four key endpoints: HADS-A, HADS-D, AIS trajectory, and objective sleep parameters from actigraphy, yielding a significance threshold of α = 0.0125 (0.05/4). For EEG spectral analyses, given the exploratory nature and high dimensionality (5 frequency bands × 6 timepoints), the Benjamini–Hochberg procedure will control the false discovery rate at q < 0.05.

A three-step approach will be used to identify predictors of POSD: (1) Univariate screening (*P* < 0.10) for 30 EEG variables (5 bands × 6 timepoints); (2) LASSO regularization (10-fold CV) to select independent predictors; (3) Multivariable logistic regression reporting ORs and 95% CIs.

The main analysis will adhere to the intention-to-treat methodology. To address missing data, multiple imputation via chained equations will be utilized, generating 20 imputations under the assumption that data are missing at random. Sensitivity analyses will incorporate pattern-mixture models to account for mechanisms where data are missing not at random. The per-protocol analysis will exclude cases with significant protocol deviations. Effect sizes will be reported as Cohen’s d, alongside 95% confidence intervals.

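### Peak frequency is scored as the in-band maximum of the raw PSD, so on a falling spectrum a band without a strong rhythm of its own is usually scored at or near a band limit

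*Protocol article*

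**What the plan says.** Section 2.7.2 (Secondary outcomes) lists two quantitative EEG parameters, absolute band power and peak frequency. The second is defined in one line: "Peak frequency: The frequency at which maximum PSD occurs within each band". The bands are "delta 1–4 Hz, theta 4–8 Hz, alpha 8–12 Hz, beta 12–25 Hz, and gamma 25–45 Hz", so each shares a limit with its neighbour.

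Section 2.5 (EEG power spectrum processing) gives the estimator: "EEG power spectral density will be estimated using the multitaper method (15 tapers, time-half bandwidth product = 8) with a 4-s window length". On filtering it says "The bandpass filter (0.5–45 Hz) will be applied as a zero-phase filter using forward-reverse filtering to avoid phase distortion". It mentions no whitening and no removal of the background slope.

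Section 2.11 (Statistical analysis) names the modelled EEG quantity as "EEG spectral power across five bands (delta, theta, alpha, beta, and gamma) at six time points (T0–T5", and the predictor screen is "for 30 EEG variables (5 bands × 6 timepoints". Peak frequency appears in neither.

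**The concern.** A peak frequency should say where an oscillation sits. The stated rule instead takes the largest PSD value in the band, whether or not the spectrum has a peak there. If the spectrum falls across a band, its largest value is at the lower limit, which the investigators chose. If a strong rhythm lies just outside the band, its flank can place the maximum at the shared limit.

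In such bands the score is close to a constant set by the band table, or it follows the background slope or the power next door. At stake is whether a declared secondary parameter measures what its name says. The six timepoints make this relevant: T0, T1 and T5 are recorded outside general anaesthesia and T2 to T4 during or at the end of it, so slope and alpha power may well differ between them.

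**Working it through.** **The article states no peak-frequency figure, so there is none to reproduce.** The check runs the stated pipeline on signals whose content is known.

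**Inputs from the article:** 500 Hz sampling; zero-phase 0.5–45 Hz filter; 4-s windows with a 2-s step; 15 tapers; time-half-bandwidth product 8; the five bands; maximum PSD within each band.

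**Assumptions not in the article:** background power proportional to 1/f^x, with x from 0.5 to 2; 60-s records; a 4th-order Butterworth filter; in some settings an alpha rhythm near 10 Hz at 3 or 5 times the local background. Each setting used roughly 100 to 200 records, and the ranges below include the spread between repeated runs.

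**Step 1, bandwidth.** W = NW/T = 8/4 = 2 Hz, so the full smoothing width is 2 × 2 = 4 Hz. Theta (8 − 4 = 4 Hz) and alpha (12 − 8 = 4 Hz) are no wider than this, and delta (4 − 1 = 3 Hz) is narrower.

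**Step 2, benchmark.** If the score were spread evenly over a band, the share within 0.5 Hz of the lower limit would be 0.5/width: delta 0.5/3 = 17%, theta and alpha 0.5/4 = 12.5%, beta 0.5/13 = 4%, gamma 0.5/20 = 2.5%.

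**Step 3, no rhythm, article's settings.** Share within 0.5 Hz of the lower limit:

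| Band | x = 0.5 | x = 1 to 2 |
|---|---|---|
| delta | 1–5% | 91–100% |
| theta | 99% | 100% |
| alpha | 86–87% | 98–100% |
| beta | 71–73% | 94–100% |
| gamma | 48–58% | 73–96% |

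Gamma varies most between runs; one set gave 90–93% at x = 1 to 2. Delta at x = 0.5 is the exception to edge scoring, but those signals contain no delta rhythm, so the interior value is not an oscillation either.

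**Step 4, one alpha rhythm added.** Alpha is read correctly (median 9.75–9.9 Hz with the 5× rhythm, none on an edge). Beta is scored within 0.5 Hz of 12 Hz in 100% of records at every slope, and theta on one of its edges in about 100%. Which theta edge depends on the assumptions. With a 3× rhythm, theta goes to 8 Hz in 97% of records at x = 0.5, 2% at x = 1 and 0% at x = 1.5 and 2. With a 5× rhythm at x = 1 it does so in 56%.

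**Step 5, true rhythms in other bands.** With rhythms at 6 Hz (2×), 10 Hz (5×) and 18 Hz (3×), beta still returned exactly 12 Hz in 97–100% of records and theta returned an edge in 51–99% (x = 1 to 2). Alpha was on its edge in 1%, 8% and 54% at x = 1, 1.5 and 2. So the rule can also miss rhythms that are present.

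**Step 6, narrower bandwidth.** With NW = 2 and 3 tapers, W = 2/4 = 0.5 Hz. No rhythm, x = 1 to 2: one run gave lower-limit shares of theta 81–98%, alpha 64–86%, beta 54–71% and gamma 44–58%. Another gave gamma as low as 28% at x = 1. At x = 0.5 the shares were theta 57%, alpha 41%, beta 33% and gamma 18%. All are below step 3 and well above step 2. With an alpha rhythm and x = 1 to 2, beta stayed at 12 Hz in 98–100%.

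**The case against.** **No planned analysis is shown to use the parameter.** Section 2.11 models spectral power, and the predictor screen has one variable per band and timepoint, which leaves no place for peak frequency beside power. This stands. A reader might infer that edge values would become mechanistic evidence for taVNS; the article names no test by which that would happen.

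**The awake-versus-anaesthetised contrast is a time effect shared by both arms.** This also stands. A reader might infer false evidence of a treatment effect. But a between-arm difference in the score would still reflect some spectral difference between the arms; the fault is that it would be labelled a frequency shift.

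**Bandwidth drives much of the size, and the move of theta to 8 Hz is not general.** Both stand. Steps 3 and 6 show the dependence on bandwidth. Step 4 shows that theta moves to 8 Hz only with a shallow slope or a large alpha rhythm.

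**The spectra are invented.** The article gives none, so every percentage is conditional. The direction is not in doubt: the maximum of a decreasing function on an interval lies at its lower end.

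**This is a condensed article, and edge handling could sit in an analysis plan that is not shown.** This does not answer the point. The definition is a complete scoring rule as written, and following it produces the edge values.

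**Conclusion.** The point holds in a limited form. On a falling spectrum, the stated definition usually scores a band limit in bands without a strong rhythm of their own. The evidence is firmest for theta and beta, which are scored at an edge in nearly all simulated records at slopes 1 to 2, with or without an added alpha rhythm. It holds for alpha when no rhythm is present. It is weaker and less stable for gamma, and at slope 0.5 it does not hold for delta. The 2 Hz half-bandwidth makes matters worse but is not the sole cause.

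It would go too far to say that the outcome is uninformative everywhere: a clear alpha rhythm on its own is located correctly. The consequence is confined to an exploratory secondary EEG parameter. The primary outcome, the sample size and the planned band-power models do not depend on it. It is worth correcting because the parameter is declared and the repair is cheap.

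**What to change.** In section 2.7.2, define peak frequency as the frequency of a local maximum of the PSD that lies strictly inside the band and rises above the background, for example a 1/f background fitted on log-log axes over 1–45 Hz. Record 'no peak' when there is none. The background criterion is needed because noise alone can create small interior maxima. Report the share of records with a detectable peak by arm and timepoint, and compare peak frequency only in bands where most records have one, which may in practice be alpha alone. A narrower multitaper bandwidth for this parameter would help, but is not sufficient alone.

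The cost is a sentence or two of protocol text and a few lines of code, with no new data; it is best settled before the EEG data are examined. The downside is that some band-by-timepoint cells will have no value, so the parameter will be reported for fewer bands.

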### Safety evaluation

2.8

Safety monitoring will be conducted throughout the hospitalization period. Adverse events (AEs) and serious adverse events (SAEs)–defined per ICH-GCP guidelines (events resulting in death, life-threatening conditions, significant disability, prolonged hospitalization, or congenital anomalies)–will be meticulously documented and monitored until resolution.

Potential taVNS-related AEs include:

(1) Dermatological reactions (contact dermatitis, local paresthesia, electrode site irritation);

(2) Cardiovascular effects (hypotension, hypertension, bradycardia, tachycardia);

(3) Neurological symptoms (dizziness, headache);

(4) Respiratory events (oxygen desaturation); and

(5) Gastrointestinal disturbances (nausea, vomiting).

Serious adverse events will be reported to the ethics committee, principal investigator, and relevant regulatory authorities within 24 h per institutional policy. An independent Data Monitoring Committee (IDMC) will conduct scheduled safety reviews at 50% enrolment and biannually thereafter, focusing on SAE rates without efficacy analysis to preserve the overall type I error rate.

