**FIGURE 1 F1:**
[figure not shown]
Flowchart of the study design.

**TABLE 1 T1:** Study schedule for data measurements.

Study period											
	Enrollment	Allocation	Post allocation								
Timepoint	Pre1	0 d	T0	T1	T2	T3	T4	T5	POD 1	POD 2	POD 3
Enrollment											
Eligibility screen	X										
Informed consent	X										
Random allocation		X									
Interventions											
Active taVNS				X				X			
Sham taVNS				X				X			
Assessments											
Baseline data	X	X									
EEG			X	X	X	X	X	X			
AIS	X								X	X	X
HUAWEI WATCH GT2	X								X	X	X
QoR-15	X								X		
NRS	X								X		
PSQI	X										
HADS-A	X								X	X	X
HADS-D	X								X	X	X
Adverse events	Record at any time at any time at any time										

Pre1 for preoperative day 1, T0, preoperative baseline (5 min before taVNS); T1, preoperative sustained stimulation period (20–30 min taVNS); T2, post-induction (5 min after intubation); T3, intraoperative maintenance (20 min after incision); T4, peri-extubation (end of surgery); T5, postoperative sustained stimulation (20–30 min post-taVNS). POD 1–POD 3 for postoperative days 1–3; taVNS, transcutaneous auricular vagus nerve stimulation; EEG, electroencephalography; AIS, Athens Insomnia Scale; QoR-15, 15-item Quality of Recovery questionnaire; NRS, numeric rating scale; PSQI, Pittsburgh Sleep Quality Index; HADS-A/HADS-D, Hospital Anxiety and Depression Scale-Anxiety/Depression subscale.

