### Anesthesia protocol

2.4

Standard monitoring will include electrocardiography, pulse oximetry, and noninvasive blood pressure. General anesthesia will be initiated using intravenous administration of propofol (2 mg/kg), sufentanil (0.5 μg/kg), and rocuronium (0.6 mg/kg). Mechanical ventilation will be administered in volume-controlled mode with an inspiratory to expiratory ratio of 1:2, a respiratory rate of 10–12 breaths per minute, and a tidal volume of 6–8 mL per kg of predicted body weight. End-tidal CO_2_ levels will be kept between 35 and 45 mmHg. Anesthesia will be sustained using continuous infusions of remifentanil (0.05–0.15 μg⋅kg^–1^⋅min^–1^) and propofol (50–100 μg⋅kg^–1^⋅min^–1^), supplemented with intermittent rocuronium boluses (0.2 mg⋅kg^–1^) as needed. The ConView anesthesia consciousness monitor (Model YY-105, Zhejiang Puke Medical Technology Co., Ltd., China) will be utilized to evaluate anesthetic depth. This apparatus produces the anesthesia consciousness index (Ai), a quantitative metric derived from the analysis of frontal EEG signals. The Ai scale spans from 0, representing the deepest level of anesthesia, to 100, indicating full wakefulness. This scale exhibits high reliability and a significant correlation with the bispectral index (BIS) (21). Throughout the surgical procedure, the anesthesia consciousness index (Ai) will be maintained within the range of 40–60. Extubation will be performed when patients demonstrate regular spontaneous respiration, adequate minute ventilation, and the ability to follow commands. Patients are transferred to the post-anesthesia care unit (PACU) when their Steward Recovery Score is 5 or above. Upon arrival in the PACU, patient-controlled analgesia (PCA) will be initiated using a consistent regimen: sufentanil at a dosage of 1.5 μg/kg combined with tropisetron 6 mg in 100 mL of normal saline, administered via an electronic PCA pump. The pump settings will be programmed as follows: a continuous background infusion rate of 2 mL/h, a PCA bolus dose of 1 mL, and a lockout interval of 15 min. Rescue analgesia will be standardized such that patients with a Numeric Rating Scale (NRS) pain score greater than 5 at rest will receive intravenous flurbiprofen 50 mg as an additional analgesic. To minimize environmental confounding, all participants will be admitted to a single, dedicated gynecology ward unit following surgery. This unit features uniform room configurations (two beds per room, standardized layout), consistent lighting protocols (lights out at 22:00, dimmed night lighting), and noise control policies (designated quiet hours 22:00–06:00). The same nursing team, trained in ERAS protocols, will provide postoperative care to all participants, ensuring consistency in care delivery, visitor management, and nighttime disturbance patterns.

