### Data collection and management

2.9

Outcome and safety variables will be systematically collected across three distinct phases: preoperative, intraoperative, and postoperative. During the preoperative phase, demographic data, medical history, surgical information, laboratory values, and baseline assessments, including AIS, HADS, NRS for pain, and QoR-15, will be recorded at the enrolment visit immediately preceding the initial taVNS session. In the intraoperative phase, data on the duration of anesthesia and surgery, tracheal intubation time, estimated blood loss, fluid infusion volume, medication administration, and continuous EEG parameters will be meticulously documented. Postoperatively, the AIS and HADS will be assessed in the evenings of POD 1, 2, and 3. Additionally, the QoR-15 and NRS pain scores, both at rest and during movement, will be evaluated on the morning of POD 1, alongside the documentation of clinical outcomes and any adverse events.

All data will be systematically recorded using standardized case report forms (CRFs) and subsequently double-entered into an encrypted electronic database by two independent research assistants. A random sample comprising 10% of the CRFs, stratified according to the enrolment sequence, will undergo verification against the original medical records. The data manager will be responsible for generating queries related to missing or inconsistent values, with the principal investigator overseeing their resolution. In compliance with institutional policy and ICH-GCP guidelines, original CRFs will be securely stored in a locked cabinet with restricted access for a minimum duration of 5 years. The electronic data will be hosted on hospital servers, safeguarded by SSL encryption, automated backups, and role-based access control, ensuring access is limited to authorized study personnel.

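### No common end is fixed for detecting new adverse events: safety monitoring is tied to the hospital stay, while sleep follow-up runs to POD 3 for everyone

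*Protocol article*

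**What the plan says.** The protocol article describes AE collection in three places.

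- **Section 2.8, Safety evaluation:** "Safety monitoring will be conducted throughout the hospitalization period". The same section says that AEs and SAEs "will be meticulously documented and monitored until resolution".
- **Section 2.9, Data collection and management:** "Outcome and safety variables will be systematically collected across three distinct phases: preoperative, intraoperative, and postoperative". The end of the postoperative phase is not given. The only AE record tied to a day is the one made with the QoR-15 and pain scores, which are to be "evaluated on the morning of POD 1, alongside the documentation of clinical outcomes and any adverse events".
- **Table 1:** the AE row reads "Record at any time at any time at any time" (the repetition is probably a product of text extraction), in a schedule whose last column is POD 3.

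Other follow-up has a fixed end. Section 2.9 states that "the AIS and HADS will be assessed in the evenings of POD 1, 2, and 3". Section 2.7.2 has the watch worn through POD 3, and section 2.3 repeats the blinding question on POD 3. The Discussion describes an observation window of 3 days. No section gives a length of stay, a discharge day or a minimum stay.

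**The concern.** Discharge is not a fixed time point. If new AEs are sought only while the participant is in hospital, the period at risk of being recorded varies from one participant to the next, and the AE proportion in each arm has no common time base. The sleep outcomes do not have this problem, because their last assessment is the same calendar day for all.

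Some of the potential device-related events listed in section 2.8, such as contact dermatitis, headache or dizziness, could first appear after a patient has gone home. Such an event could go unrecorded even though the trial is still in touch with that patient for the AIS and HADS. The monitoring committee's reviews focus on SAE rates, so the window also decides what that committee can see.

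**Working it through.** There is no stated figure to reproduce, since the point depends on no sample size, power or event count. The check is a comparison of the statements.

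**Step 1. What each statement fixes about the end of AE collection.**

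| Place | Detection of new AEs | Follow-up of recorded AEs |
|---|---|---|
| Section 2.8 | While in hospital; no calendar end | To resolution |
| Section 2.9 | Postoperative phase, end not stated; POD 1 morning is the only named record | Not stated |
| Table 1 | At any time; last column POD 3 | Not stated |

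**Step 2. Do they contradict one another?** Not strictly. A POD 1 morning record and any-time recording both fit inside continuous in-hospital monitoring, and section 2.9 does not say that recording stops on POD 1.

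**Step 3. Do they give the same end?** Only if every participant stays in hospital to POD 3. Nothing in the article requires that.

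**Step 4. What follows for a single participant, on the wording of section 2.8.**

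| Discharge | AIS, HADS, watch | New AEs sought |
|---|---|---|
| After the POD 3 evening assessment | To POD 3 | To POD 3 or later |
| POD 2 | To POD 3 | To POD 2 |
| POD 1 | To POD 3 | To POD 1 |

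**Step 5. How many are affected?** This cannot be computed. The share is the proportion discharged before the end of POD 3, and the article gives no length of stay. It is none if all stay that long and could reach all participants if discharge is routinely earlier. Counting lost days would not measure lost events either: both stimulation sessions finish on the day of surgery under continuous monitoring (section 2.6), so events need not be spread evenly over the following days.

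**The case against.** The strongest reply is that this is an unstated end date in a condensed article, and that the full protocol may well hold the AE contact schedule. On a plain reading of Table 1, the AE row covers every column up to POD 3. The design also points towards an inpatient stay: a single dedicated ward with controlled light and noise (section 2.4), and evening assessments to POD 3. If patients do stay that long, nothing is lost.

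Much of this stands. A reader might infer that the three statements contradict each other; they do not. A reader might also infer that AE follow-up stops at discharge. Section 2.8 follows recorded events to resolution, so only the detection of new events could stop then.

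A further tempting inference is that quicker recovery under taVNS would shorten observation in that arm and make the device look safer. That would need a shorter stay under taVNS, discharge before POD 3, and new events arising after discharge. The article shows none of these. The rule is the same in both arms, surgeons, ward staff and assessors are blinded, length of stay is not an outcome, and section 2.11 states no between-arm AE comparison. Blinding would not remove a difference caused by a real effect on recovery, so the possibility remains, but only as a possibility.

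The appeal to condensation does not dispose of the point. The article does not leave the window out: section 2.8 states a rule, and that rule makes detection depend on length of stay.

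**Conclusion.** The point holds in a limited form. As written, the end of detection for new AEs is the participant's discharge, not a common day, and sections 2.8 and 2.9 and Table 1 do not settle on one end. For anyone discharged before POD 3, sleep follow-up would outlast AE detection.

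The size is unknown and may be zero, because it rests wholly on a length of stay that the article does not give. No bias between arms has been shown, and the primary result is not touched. This is an inexpensive improvement to safety ascertainment, not the correction of a demonstrated error.

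**What to change.** Reconcile sections 2.8 and 2.9 and Table 1 to one window: all AEs from the start of the first stimulation session to the evening of POD 3, for every randomised participant, whether or not still in hospital. Ask one AE question at each of the AIS/HADS contacts already planned for POD 1, 2 and 3. Keep the follow-up of open events to resolution. Report AE incidence by arm over this common window.

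The cost is a wording change in three places and slightly more AE data entry. No visit is added, and treatment, randomisation and sample size are unchanged.
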